## Abstract

Background: Many stroke survivors suffer from sensorimotor deficits, especially balance impairments. The purpose of this trial is to investigate whether the designed Immersive Virtual Reality training program is better in the short term (15 sessions) and in the medium term (30 sessions) than physiotherapy training with Bayouk, Boucher and Leroux exercises, with respect to static balance in sitting and standing, dynamic balance and quality of life in patients with balance impairment in stroke survivors. Methods: This study is a randomized controlled trial with two treatment arms and evaluators blinded, and a functionality treatment group in combination with specific balance exercise training according to Bayouk, Boucher and Leroux (control group) or a balanced treatment using Immersive VR. The primary outcome will be static, Dynamic balance and gait measured by Bestest Assessment Score (BESTest), Berg Scale (BBS), Pass Scale (PASS) and Time Up and Go test (TUG). The secondary outcome will be the stroke-associated quality of life using the Stroke Quality of Life Scale (ECVI-38). Conclusions: The results of this study may add new insights into how to address balance using Immersive Virtual Reality after a stroke. If the new training approach proves effective, the results may provide insight into how to design more comprehensive protocols in the future for people with balance impairments after stroke.

## 1. Introduction

Worldwide, stroke is considered the second leading cause of death, and the third of death and disability combined. Although advances in treatment encourage a decrease in mortality among subjects who have had a stroke, among survivors, there is a great functional impairment, which is one of the main causes of disability, due to the persistence of symptoms in the long term [1,2,3].

Cerebrovascular accident (CVA) or stroke causes a sudden disruption of physiological brain function leading to impairment of functional brain networks [4]. The alteration of balance in stroke that occurs after having suffered brain injuries affects mainly the parieto-temporal or parieto-vestibular areas. This situation can cause a significant problem for the independence of these patients since they present a loss of the sense of touch, protective reactions and proprioceptive sense; all these losses are correlated with the ability to balance, which will affect mobility, and it is the main consequence of falls in subjects with Ictus [5].

Through sensory integration, the brain organizes somatosensory, visual and vestibular information and provides crucial information that is used for complex motor skills (maintaining balance and walking interacting with the environment) [6,7]. This sensory integration could be the key to promoting recovery through repetitive goal-oriented intensive therapeutic interventions and appropriate non-invasive brain stimulation [8].

Physiotherapy intervention programs in patients post-stroke must develop strategies to assess functional deficit, prevent maladaptive plasticity and maximize functional gain. For relearning and functional training, the intervention activities require motor control and must comply with the following principles: movements close to normal, muscle activation, movement conduction, focused attention, repetition of desired movements, training specificity, intensity and transfer [9,10,11]. The most widely used conventional physiotherapy intervention programs in the hospital setting are based on these principles.

Studies show that the combination of conventional physiotherapy intervention protocols with the use of systems of training through Virtual Reality (VR) optimizes the results in the recovery of the functional deficit of patients post-stroke [12,13,14,15,16,17].

Most of the systems included in the current literature are based on the use of video games or fictitious digital environments, such as Non-Immersive Virtual Reality, where the sensory inputs received by the patient do not correspond to reality, a situation that makes it difficult to adequate sensory integration [18,19,20,21].

In the absence of clarity in the use of VR terminology, we find great differences between systems labeled VR and the level of immersion, the extent to which virtual information is mixed with that of the real world and the type of input devices used [22].

A non-immersive virtual environment is commonly experienced in two dimensions, and subjects can interact via an avatar [23] (allocentric perspective) with the environment displayed on a screen [24].

In contrast, in an immersive virtual environment, subjects could egocentrically operate in a simulated world environment [25], allowing interaction with a visual perspective in real-time based on the position of the body/head, where the subject himself is who interacts with the scenarios and proposed tasks.

On the other hand, there are few previous studies using Immersive Virtual Reality in general; this may be because non-immersive video game systems developed for entertainment are less expensive, which has made this modality more accessible for possible rehabilitation interventions in stroke patients [26]. If we focus on Immersive VR, it has recently started being used as a tool to allow people with sensorimotor deficits to practice challenging skills in a safe environment [17,20,21,26,27,28,29]. 

There are studies that have demonstrated the effectiveness of the application of this immersive technology in older adult patients with cognitive impairments, where patients had moderate emotional learning and showed greater confidence in multisensory integration for learning [27,30,31,32], and also in Parkinson’s disease [28,33,34,35] and on the balance, mobility and fatigue in multiple sclerosis [29,36]. In addition, the use of gamified Immersive Virtual Reality adapted to the patient obtained good results in the rehabilitation of neglect symptoms after a stroke. [37]. Neural activity has also been seen to increase after Immersive VR intervention, particularly in brain areas involving activated mirror neurons, as in the primary motor cortex [27,31,32,38].

This study aims to determine whether the designed Immersive VR training program is better in the short term (15 sessions) and medium term (30 sessions) than physiotherapy training with exercises by Bayouk, Boucher and Leroux [39] regarding the change of measures related to static sitting, and standing balance and dynamic balance in post-stroke patients.

Secondary objectives verify the impact on quality of life and safety of the application of this type of technology.

## 2. Materials and Methods

### 2.1. Study Design and Setting

The RCT is a parallel-group design, with 1:1 randomization to a designed Immersive VR program related to the improvement of motor control during static, dynamic balance and gait in patients post-stroke, compared with usual physiotherapy care intervention, applying exercises for static and dynamic balance according to Bayouk, Boucher and Leroux [39]. This protocol follows the SPIRIT 2013 [40] recommendations for clinical trial protocols Identifier NCT04379687. The study flow is outlined in Figure 1.

This study is conducted at the Physiotherapy Unit of the Miguel Servet University Hospital in Zaragoza.

### 2.2. Participants

Eligible patients who agree to participate will meet the following inclusion criteria: Adults older than 18 and younger than 80 years old, with a diagnosis of stroke with hemiparesis or hemiplegia post-acute stroke admitted to hospital, and with a minimum score of 2 points in item 3.2 of the BBS (Berg Balance Scale) [41], which establishes that the patient can remain seated for 30 s without help. Exclusion criteria include aphasia, scores greater than 45 on the Mississippi Aphasia Screening Test [42]; cerebellar pathology; hemineglect or previous neurological disorder; visual disorders that prevent the use of VR glasses; moderate cognitive impairment, scores less than 24 on the MMSE (Mini-mental State Examination) [43]; previous musculoskeletal disorders that hinder or prevent balance in sitting and standing or gait; vestibulocochlear disease; spinal cord injury or disease; systemic peripheral neuropathy; persistent phobic postural dizziness; migraine; Ramsay Hunt Syndrome; and psychiatric disorders. 

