### 2.3. Randomization of Subjects

Eligible patients recruited by nursing will be randomized as they are referred for physiotherapy treatment by the supervisor of the Physiotherapy Unit to one of the two trial groups after signing the informed consent. The sequence will be performed randomly in a 1:1 allocation to the Immersive VR training group and the Bayouk, Boucher and Leroux physical therapy training group for balance, using a computerized random allocation program.

This sequence will be prepared by an investigator not involved in the allocation of patients. 

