### 2.4. Intervention Protocol/Procedure

Eligible subjects will be identified by the stroke diagnosis; they will be patients admitted to the Neurology Service of the Miguel Servet Hospital in Zaragoza. In an initial visit, the nursing staff will inform those potentially eligible, who will be pre-selected based on whether or not they meet the inclusion and exclusion criteria for this study. Likewise, they will proceed to explain this study to the included subjects, collect the willingness to participate and provide the informed consent document.

Prior to random assignment, two physiotherapists who are experts in neurological assessment will evaluate the outcome variables for each participant. Subsequently, patients will be randomly assigned to the control group or the experimental group in a 1:1 ratio, computerized random assignment program. The patient will be informed that in subsequent evaluations, they do not reveal to the evaluators to which group they have been assigned.

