### 2.7. Outcomes

All study participants will be evaluated before starting treatment (baseline) at 15 sessions and 30 sessions. The outcome measures are compiled in Table 3. 

The parameters of balance in sitting and standing static and dynamic and in the temporospatial and kinematic parameters of gait will be obtained from the following tests and scales. 

For static balance and functional mobility, the PASS Spanish version [21,45], the BBS [34] and the BESTtest [46] have been used. 

BBS has a high relative reliability with interrater reliability estimated at 0.97 (95% CI 0.96 to 0.98) and intra-rater reliability estimated at 0.98 (95% CI 0.97 to 0.99). The absolute reliability of the BBS varies across the scale, with minimal detectable change with 95% confidence varying between 2.8/56 and 6.6/56 [41].

PASS is a 12 items performance-based scale used for assessing and monitoring postural control following a stroke. It consists of a 4-point scale where three items are scored from 0 to 3, and the total scoring ranges from 0 to 36 [45]. The minimal detectable change in subacute stroke is 2.22 points [47]; in acute stroke, 1.8 points [48]; and in chronic stroke, it is 3.2 points [49].

BESTest consists of 27 tasks, with 36 items in total. Each item is scored based on ordinal scale scoring from 0 to 3, where 3 represents best performances, and 0 represents worst performances. Scores for the total test are provided as a percentage of total points [50]. Additionally, the minimal detectable change in subacute stroke is 7.81 points [50]. 

To measure dynamic balance and gait, the TUG test [51] and the 10 m walk test [52] will be used. 

In the TUG test, the patient rises from a chair, walks three meters in a straight line, turns, returns and sits down while the examiner times the time required to perform the test. In addition, the TUG assesses the risk of falling. A score of less than 10 s indicates a low risk of falling, between 10 and 20 s indicates frailty with a higher risk of falling, and more than 20 s a high risk of falling [51]. The minimum detectable change in stroke is estimated at 2.9 s [53].

10 m walk test has an excellent interrater reliability estimated ICC = 0.87 to 0.88, and an excellent interrater reliability ICC = 0.998. The minimum detectable change is set at 0.05m/s, and a substantial change is set at 0.10m/s [52].

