### 2.11. Data Management and Statistical Analysis

Sample size: For instance, to achieve 80% power to detect differences in contrast to the null hypothesis H₀, mean difference in BESTest is equal to the limit of superiority, using a one-sided Student’s t-Test (superiority) for two independent samples, taking into account that the significance level is 5%, and assuming that the superiority limit is 7.81 units, as suggested in the article by Candance, et al., [55]. Additionally, the proportion of patients in the control group with respect to the total is 50%; it will be necessary to include 18 patients in the control group and 18 in the experimental group, a total of 36 patients in this study. Considering that the expected percentage of dropouts is 20%, it would be necessary to recruit 22 patients in the control group and 22 patients in the experimental group, a total of 44 patients in this study.

Patient characteristics and comparisons at baseline: To assess the comparability of the two groups, the characteristics of the patients assigned to each group will be presented in a table. Discrete variables will be summarized as frequencies and percentages. Continuous variables and time intervals will be summarized using means, standard deviation, or median and interquartile range. Both groups need to be homogeneous at baseline.

The statistical analysis will be carried out by an intention-to-treat analysis.

Analysis of the main objectives: Normality tests of the dependent variables were undertaken using the Kolmogorov–Smirnov test. The description of the results of the dependent variables was also performed, using either the mean and the standard deviation or the median and interquartile range, depending on the adjustment of these variables to normality. 

To respond to the main objective, with each primary result, hypothesis tests will be performed (where the alternative hypothesis is the greater efficacy of the experimental treatment compared to the conventional one), and estimates will be provided by 95% confidence intervals. In addition, the t-Student test will be used for independent samples in the parametric case and the Mann–Whitney U test for the non-parametric case.

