	Hypertension	Yes/no
	Hypercholesterolemia	Yes /no
	Diabetes mellitus	Yes /no
	Tabaco habit	Yes /no
	Habitual consumption of stimulants or toxic substances	Yes /no
	Chronic drug use	Yes /no
	Mississippi Aphasia Screening Score	Score
	Mini-mental State Examination Score	Score
	Days of hospitalization	Number of days

BMI: Body Mass Index.

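### Time from stroke onset is not in the listed baseline data and not in the stated primary test, so its variation stays in the error term and a chance imbalance would not be reliably seen or corrected

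*Protocol article*

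**What the plan says.** - **Eligibility (section 2.2).** Patients enter "with a diagnosis of stroke with hemiparesis or hemiplegia post-acute stroke admitted to hospital". Age, the sitting item of the Berg scale, the aphasia score and the MMSE have numeric limits; the stroke phase has none. Patients with "hemineglect or previous neurological disorder" are excluded.
- **Source (section 2.4).** Recruitment is from one inpatient service: "they will be patients admitted to the Neurology Service of the Miguel Servet Hospital in Zaragoza".
- **Baseline data (Table 5).** The list covers age, gender, BMI, vascular risk factors, habits, drug use, and the aphasia and MMSE scores. It closes with "Days of hospitalization", given as a number of days. There is no onset date or time since stroke. Table 3 marks this group of variables at T0 only, and section 2.10 exempts them from the later assessments.
- **Allocation (section 2.3).** "The sequence will be performed randomly in a 1:1 allocation", "using a computerized random allocation program". No stratification factor is named.
- **Analysis (section 2.11).** Each primary outcome is compared by an independent-samples t-test or a Mann–Whitney U test, with no covariate. The section adds: "Both groups need to be homogeneous at baseline".
- **Sample size (sections 2.7 and 2.11).** The superiority limit is 7.81 BESTest units. Section 2.7 gives the same figure as the minimal detectable change in subacute stroke.

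**The concern.** Patients assessed at different intervals after a stroke may be expected to change by different amounts over 30 sessions, whichever arm they are in. If so, a comparison that ignores the interval carries that spread as noise, and in a trial of this size chance can leave one arm earlier after stroke than the other. The article asks for homogeneous groups, but the data it lists do not directly allow that check for time since onset, and the stated test cannot correct an imbalance.

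A second, smaller matter is the sample size. It rests on a figure for subacute stroke, while neither the entry criteria nor the baseline list establishes the phase of those enrolled. Readers could not tell whether 7.81 fits them.

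**Working it through.** **Step 1. The plan's own figure.** Section 2.11 gives 18 per arm for 7.81 BESTest units, one-sided 5% and 80% power. No SD is stated, so 18 cannot be reproduced directly. Taking 7.81 as the difference to detect (an assumption), the SD can be solved for:

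- Normal approximation: SD = 7.81 × √(18/2) / (1.645 + 0.842) ≈ 9.42.
- Noncentral t: 18 is the smallest sufficient n for an SD between 8.96 and 9.23.

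I use 9.23 below. The recruitment figure of 22 per arm matches 18 × 1.2 = 21.6, rounded up.

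**Step 2. Probability of a chance imbalance.** For a baseline factor left to simple 1:1 allocation, the standardised difference between arms has SE = √(2/n).

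| n per arm | SE | P(difference > 0.5 SD) | P(difference > 0.25 SD) |
|---|---|---|---|
| 18 | 0.333 | 2(1 − Φ(1.50)) = 0.134 | 0.45 |
| 22 | 0.302 | 2(1 − Φ(1.66)) = 0.097 | 0.41 |

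Differences in either direction are counted.

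**Step 3. What a 0.5 SD imbalance does.** The shift in the unadjusted comparison is r × 0.5 outcome SDs, where r is the correlation of time since onset with the outcome. The article gives no r; 0.3 to 0.5 is assumed.

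- r = 0.3: 0.15 SD, or 0.15 × 9.23 ≈ 1.4 BESTest units (18% of 7.81).
- r = 0.5: 0.25 SD, or 0.25 × 9.23 ≈ 2.3 BESTest units (30% of 7.81).

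**Step 4. What adjustment gains.** The variance removed is r²: 0.3² = 9% to 0.5² = 25%, provided that time since onset is independent of the baseline score. To show the effect on power I vary R², the share of outcome variance explained, from 0.05 to 0.30 (assumed), at 18 per arm. The answer depends on whether the unstated planning SD already contains this variation.

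| R² | SD contains it: power after adjustment | SD omits it: power without adjustment | SD omits it: n per arm for 80% |
|---|---|---|---|
| 0.05 | 82% | 78% | 19 |
| 0.10 | 84% | 76% | 20 |
| 0.20 | 87% | 72% | 23 |
| 0.30 | 91% | 67% | 26 |

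The adjusted SD is 9.23 × √(1 − R²); the inflated SD is 9.23 / √(1 − R²). The degree of freedom spent on the covariate is ignored, so the gains are very slightly optimistic.

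**Step 5. Can the listed data stand in?** Tables 3 and 5 together support reading the hospital-days item as a count taken at T0. The article does not say so, and the item runs from admission, not from onset. If it were total length of stay, part of it would fall after randomisation, and it could not serve as a baseline covariate.

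**The case against.** The case on the other side is substantial.

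- **Time since stroke is bounded in practice.** A reader might infer that patients days and months after stroke are mixed without limit. The text does not support this. Entry is confined to post-acute inpatients of one neurology service without earlier neurological disease. The chronic phase is largely irrelevant, and a narrow range would tend to lower r.
- **A proxy is collected.** A reader might infer that an imbalance could not be detected at all. That goes too far: the hospital-days item is scheduled at T0, and patient characteristics are to be tabulated by arm. Balance scores are also measured before allocation, so unequal starting function would show. What stands is that the proxy is partial and its count undefined.
- **Detectable change is not rate of recovery.** Section 2.7 reports for the PASS: "The minimal detectable change in subacute stroke is 2.22 points [47]; in acute stroke, 1.8 points [48]; and in chronic stroke, it is 3.2 points". A reader might take this as proof that recovery differs by phase. Minimal detectable change reflects measurement error, and the three values come from three sources. They do not show that time since onset drives change here. Nor is any analysis planned that applies these thresholds to individual patients, so nothing needs correcting there.
- **Silence on stratification.** An article condenses a fuller protocol, so a missing stratification statement is not a fault. The point rests on the data list and the test, which the article does state.
- **The size is generic.** The 10 to 13% applies to any unstratified factor in a trial this small, and r is assumed. Both are true. If the planning SD already contains the variation, there is no loss against plan, only a gain forgone.

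**Conclusion.** The point holds as an inexpensive improvement in precision and in protection against chance imbalance. It is not evidence of bias: a reader might infer a systematically distorted comparison, but randomisation keeps it unbiased on average.

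Time from onset to baseline is missing from an itemised baseline list, and the stated primary test leaves its variation in the error term. A difference between arms above 0.5 SD would arise in about 10% (22 per arm) to 13% (18 per arm) of such trials. Its consequence, 0.15 to 0.25 outcome SDs, and the 9 to 25% of residual variance removable both rest on an assumed correlation of 0.3 to 0.5. The conversion to BESTest units and the power figures rest further on an SD solved backwards from 18 per arm. The article gives none of these quantities, so the true effect could be smaller.

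**What to change.** 1. Add the date of stroke onset to Table 5, taken from the admission record, and derive days from onset to baseline assessment.
2. Report that interval by arm with the other baseline characteristics. Its distribution also shows whether the subacute 7.81 figure fits the patients enrolled.
3. Replace the unadjusted primary comparison with an ANCOVA that includes the outcome's baseline score and days from onset to baseline. Fix the form of the covariate before data are compared by arm.
4. Optionally, if recruitment has not begun, stratify the random list on a two-level split of days from onset, with permuted blocks. If it has begun, steps 1 to 3 suffice, provided the date is retrieved for every patient already enrolled.

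The cost is one chart item per patient and one model covariate, with no added visit, test or staff. The optional stratified list makes allocation slightly more complex; two strata are workable with 44 patients.

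### Patients who can only sit may enter, but the walking tests listed as primary give no value for a non-walker and the plan assigns none; leaving such patients out would tend to hide a benefit

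*Protocol article*

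**What the plan says.** **Entry.** Section 2.2 admits inpatients with post-stroke hemiparesis or hemiplegia "with a minimum score of 2 points in item 3.2 of the BBS (Berg Balance Scale", "which establishes that the patient can remain seated for 30 s without help". No criterion asks for standing or walking. The one exclusion that mentions gait is for "previous musculoskeletal disorders that hinder or prevent balance in sitting and standing or gait", so inability to walk because of the stroke does not exclude a patient. Section 2.6 has VR training progress from sitting to ambulation, so patients who do not yet walk are expected.

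**Outcomes.** Section 2.7 states: "To measure dynamic balance and gait, the TUG test [51] and the 10 m walk test [52] will be used". In the TUG, "the patient rises from a chair, walks three meters in a straight line, turns, returns and sits down" while being timed. The 10 m walk test is interpreted in m/s. Table 3 lists both as primary at T0, T1 and T2. The abstract's primary list ends with "Pass Scale (PASS) and Time Up and Go test (TUG") and does not include the 10 m walk test.

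**Analysis.** Section 2.11 compares each primary result between arms by an independent-samples t-test or, in the non-parametric case, a Mann-Whitney U test. It adds: "The statistical analysis will be carried out by an intention-to-treat analysis". No section shown gives a score, rank or analysis population for a patient unable to do a walking test.

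**The concern.** Entry criteria, outcomes and tests do not fit together. A patient who cannot rise and walk produces no TUG time, and an intention-to-treat statement does not create one. If the stated tests are run on recorded seconds, or on recorded speeds with non-walkers left blank, only walkers contribute.

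Walking at T1 or T2 occurs after randomisation and is something the training is meant to change. An arm that gets more patients walking adds its newest and slowest walkers to its own mean, while the comparable patients in the other arm are absent. Randomisation does not protect that comparison. What is at stake is a missed or understated benefit on gait, together with a gait analysis that is intention-to-treat in name only.

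**Working it through.** **The plan's own figure.** Section 2.11 gives 18 per arm (22 recruited) for BESTest, one-sided 5%, 80% power, with 7.81 units as the superiority limit. It states no SD and no expected true difference, so 18 cannot be reproduced. A one-sided two-sample t-test with 18 per arm has 80% power at a standardised difference of 0.846. That value is used below only as an illustrative effect; the protocol claims no power for gait.

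**Assumptions that are not in the documents.**
- Walking ability is a latent normal variable: N(0, 1) in controls and N(d, 1) in the experimental arm.
- A patient below a threshold t cannot walk and has no value. The threshold is t = Φ⁻¹(p), where p is the share of controls unable to walk at the visit.
- p is varied from 10% to 50%.

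**Step 1: shrinkage of the difference.** The mean among walkers in an arm with mean m is m + λ, where λ = φ(t − m) / [1 − Φ(t − m)]. For a true d = 0.5:
- p = 30%, t = −0.524: controls 0.497, experimental 0.779, difference 0.28.
- p = 50%, t = 0: controls 0.798, experimental 1.009, difference 0.21.

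These are in SDs of the full population, so 44% to 58% of the raw difference is lost. Walkers are less spread out: the variance among them is 1 + (t − m)λ − λ², which gives a pooled SD of about 0.76 at 30% and 0.66 at 50%. In walkers' own SD the effect is 0.282/0.756 = 0.37 and 0.211/0.659 = 0.32, a loss of about 25% to 36%.

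**Step 2: power.** Simulation with 18 per arm, d = 0.846, one-sided 5%. In the last column non-walkers are kept and tied at the worst rank.

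| Controls unable to walk | Mean number of walkers, control / experimental | Walkers-only t-test | Worst-rank Mann-Whitney, all patients |
|---|---|---|---|
| 0% | 18.0 / 18.0 | 0.81 | 0.78 |
| 10% | 16.2 / 17.7 | 0.71 | 0.78 |
| 20% | 14.4 / 17.2 | 0.62 | 0.78 |
| 30% | 12.6 / 16.5 | 0.53 | 0.76 |
| 40% | 10.8 / 15.5 | 0.44 | 0.76 |
| 50% | 9.0 / 14.5 | 0.35 | 0.76 |

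Repeat runs differ by one or two percentage points, hence the rounded ranges of about 70% to 35% and 75% to 78%.

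**Step 3: fewer patients or selection?** With the effect held at 0.846 SD and only the numbers reduced, power is 0.67 at 13 per arm and 0.53 at 9 per arm. The walkers-only results at 30% and 50% are 0.53 and 0.35. The further fall comes from selection.

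**Step 4: no true effect.** At 30% and 50% non-walkers the rejection rate is 0.044 and 0.045 for the walkers-only t-test, and 0.048 and 0.044 for the worst-rank test. The distortion runs towards masking a benefit, not towards a false claim of one.

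**The case against.** The strongest objection is that nothing shown says non-walkers are dropped. A coding rule for inability to perform could sit in an analysis plan or case report form that is not shown, and a worst-rank or 0 m/s rule would remove most of the loss. The Mann-Whitney test is already one of the two named tests, and many tied worst values would probably lead the plan to it. This stands, so the consequence must be stated conditionally. A reader might infer that the protocol commits to a walkers-only analysis and that a real benefit will be masked; the text does not support that. What remains is that the entry rule, the outcomes and the tests are all fixed in this text, and together they give no value for a patient the protocol admits.

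Four further limits also stand:
- **Share of non-walkers.** It is assumed. Training leads towards ambulation and the control exercises in Table 2 involve standing, rising or walking, so the share may fall by 30 sessions. At 10% the loss is modest (about 70% against 78%).
- **Scale of the shrinkage.** The 44% to 58% loss applies to full-population SD. In walkers' own SD it is about 25% to 36%.
- **Benchmark effect.** The 0.846 SD is back-solved from the BESTest sample size. The trial cannot be said to fall short of a planned power for gait, because none is stated.
- **Number of outcomes.** That two primary outcomes are affected rests on Table 3, since the abstract names only TUG. One is enough for the problem to arise.

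**Conclusion.** The mismatch is real: patients who can only sit are eligible, and the walking tests listed as primary have no defined value for a patient who cannot walk. If such patients are left out, the gait comparison is made in a group selected after randomisation and tends to understate a benefit in the arm that restores walking.

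The size depends on a non-walker share that the documents do not give and on the latent-normal model. The power loss runs from small at 10% non-walkers to more than half at 50% (0.81 to 0.35), while ranking non-walkers worst keeps power roughly where it would be with complete data. Type I error is not inflated. PASS, BESTest and the sample size built on BESTest are not touched, so the point concerns the gait outcomes and not the trial as a whole.

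**What to change.** In sections 2.7 and 2.11, state that:
1. At T0, T1 and T2 the assessor records whether the patient was unable to perform the test for functional reasons, separately from a test missed for any other reason.
2. Functional inability is scored 0 m/s on the 10 m walk test and given the worst rank on TUG.
3. The arms are compared with a rank-based test on all randomised patients assessed at the visit.
4. The proportion able to walk is reported by arm at each visit, and walkers-only means are given as descriptive.

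A two-part analysis (proportion walking, then speed) is a possible alternative, but its second part is again restricted to walkers.

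The cost is a few lines of wording and one tick-box. Eligibility, treatment and sample size do not change. The downside is that the TUG effect is reported as a rank shift and not in seconds. The tick-box should be in place at the visits, because the reason for a blank may not be recoverable afterwards.
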